# INTRODUCTION

The introduction of the immunosuppressive agent cyclosporine A (CsA) significantly improved the outcome of clinical renal transplantation in the eighties by reducing acute rejection rates and increasing short-term patient and graft survival. CsA and the later introduced drug tacrolimus**,** both known as calcineurin inhibitors (CNIs), are presently the cornerstones of the immunosuppressive protocols. Although CNIs have a well documented prophylactic effect against acute rejections, they contribute to the development of chronic allograft nephropathy (CAN)/interstitial fibrosis and tubular atrophy (IF/TA) leading to a substantial number of graft loss, up to 50%, in the long term (Nankivell et al., 2003)

Chronic CNI nephrotoxicity is characterized by arteriolar hyalinosis, striped interstitial fibrosis (IF) and tubular atrophy (TA), and even low doses of CNIs carry a risk of cumulative nephrotoxicity (Myers et al., 1984; Chapman et al., 2005). In order to reduce such allograft damage, current practice is to lower CNI exposure using therapeutic drug monitoring. However, complete CNI avoidance early post-transplant is associated with an unacceptably high incidence of acute rejection (Asberg et al., 2006). The mechanisms for CsA-induced nephropathy are still incompletely understood and the molecular basis remains undefined. CsA leads to activation the intrarenal renin-angiotensin system, which reduces renal blood blow through the action of angiotensin II. Angiotensin has proinflammatory and fibrogenic effects mediated by transforming growth factor beta (TGF-β) signalling. CsA also increases apoptosis in tubular and interstitial cells (Naesens et al., 2009). CNIs may also directly upregulate TGF-β in tubular epithelial cells (Vieira, Jr. et al., 1999; Johnson et al., 1999). TGF signalling may initiate epithelial-to-mesenchymal transition (EMT) leading to tubular degeneration and tubular atrophy (Hazzan et al., 2011).

Paricalcitol (19-nor-1,25-dihydroxyvitamin D2) is a synthetic, selective 3rd generation vitamin D receptor activator (VDRA) indicated for the prevention and treatment of secondary hyperparathyroidism associated with chronic kidney disease stage 3, 4, and 5 (Cozzolino & Brancaccio, 2008). Prospective studies have shown that paricalcitol effectively and safely suppresses PTH in patients with chronic kidney disease (Cheng et al., 2012), dialysis patients and transplant patients (Palya et al., 2009) with minimal effect on serum calcium and phosphorus (Ross et al., 2008; Martin et al., 1998).

*Fibrosis and inflammation*

Several other beneficial effects from VRDAs have been shown in both animal and human studies, as the vitamin D receptor is distributed not only in the bone and parathyroid, but also in other tissues, such as the kidney and the vasculature (Valdivielso et al., 2009; Andress, 2006). Several investigators have indicated that paricalcitol is renoprotective in various experimental models through its anti-inflammatory and antifibrotic actions (Tan et al., 2008; Tan et al., 2009; Mizobuchi et al., 2007; Schwarz et al., 1998). Park et al have recently showed that paricalcitol attenuates cyclosporine-induced kidney injury in rat model. (Park et al., 2010). They suggested that paricalcitol exerted an anti-inflammatory and antifibrotic effect via the inhibition of TGF-β1 signalling and thus attenuated the CsA-induced renal tubular cell apoptosis and fibrosis. They furthermore indicated that paricalcitol might be a possible renoprotective agent in a clinical setting.

In renal transplant recipients these effects may be advantageous, as preserving kidney function and reducing cardiovascular risk, is essential in the long-term care of the renal transplant recipient (Fellstrom et al., 2005b).

*Proteinuria*

Persistent proteinuria after renal transplantation is a strong and independent risk factor for renal graft failure, cardiovascular morbidity and mortality (Fellstrom et al., 2005a; Halimi et al., 2007). Both pre-clinical and clinical trials have shown that treatment with paricalcitol is associated with reduction in proteinuria (Fishbane et al., 2009; de et al., 2010; Freundlich et al., 2008; Agarwal et al., 2005; Alborzi et al., 2008). In the recently published Vital study in patients with type 2 diabetic nephropathy there was a significant reduction of proteinuria with 2 μg paricalcitol, but not with 1 μg daily (de et al., 2010). Whether this effect of paricalcitol also is present in renal transplant recipients is unknown and needs to be investigated.

*Vascular calcification*

It is suggested that coronary artery calcification and the elastic properties of aorta and large arteries are related processes (van Popele et al., 2006). The elastic property of the aorta may be assessed by measuring carotid-femoral pulse wave velocity (PWV), and aortic stiffness has been associated with atherosclerosis of the coronary arteries in older adults (van Popele et al., 2006; Weber et al., 2004). Renal transplant recipients have increased PWV, i.e. aortic stiffness, compared to a control population (Verbeke et al., 2007). We have recently shown that PWV was an independent marker for coronary artery calcification in SLE transplanted patients (Norby et al., 2011). PWV is a strong predictor of all-cause mortality in this population (Mitchell et al., 2010). Paricalcitol may have a superior protect effect on vascular calcification compared to other vitamin D analogs (Cardus et al., 2007; Noonan et al., 2008; Rodriguez et al., 2011).

In summary, paricalcitol may be beneficial for kidney transplant recipients, both in treating persistent hyperparathyroidism and bone disease and cardiovascular effects. However, the most intriguing aspect by paricalcitol treatment is the potential to prevent fibrosis in the transplanted kidney and to reduce proteinuria in this patient population. To date, the effects of paricalcitol in renal transplant recipients are largely unknown, and no randomized controlled data exists in this population.

# OBJECTIVES

Primary objective:

The primary aim of this study is to address the effect of paricalcitol on albumin excretion in renal transplant recipients.

Secondary objectives:

Important secondary endpoints are the effect of paricalcitol on:

- development of graft fibrosis and markers for fibrosis
- glomerular filtration rate
- Bone density
- Pulse wave velocity

# POPULATION

## Inclusion Criteria

In order to participate in this study the patients must meet all of the following inclusion criteria:

1. Patients over the age of 18, who have received a kidney transplant.
2. Patients with a functioning kidney transplant, defined as eGFR>30 ml/min.
3. Patient on triple immunosuppression with CNI inhibitor (cyclosporine or tacrolimus), mycophenolate mofetil or mycophenolate acid, and prednisolone.
4. Serum calcium between 2.0 and 2.6 mmol/l
5. Signed informed consent.

## Exclusion Criteria

In order to participate in the study patients must not meet any of the following exclusion criteria:

1. Patients with tertiary hyperparathyroidism previously operated with parathyroidectomy.
2. Patients treated with vitamin-D analogues after transplantation.
3. Patients who received a deceased donor kidney, from a donor >75 years.
4. Patients with a history of an allergic reaction or significant sensitivity to paricalcitol or drugs similar to study drug.
5. Use of calcimimetics after transplantation and throughout the study period.

## Recruitment and Screening

Patients will be recruited from the nephrology wards participating in the study. Patients who are considered eligible by the Investigator will have the study explained to them, and will receive the written patient information sheet (PIS). After having had the time to review the nature of the study, they will have the opportunity to ask questions to the investigational team. If, after this, the patients agree to participate, they will be asked to sign and date one original of the written informed consent form (ICF). The patients will then receive a copy of the signed and dated patient information/informed consent form. The original signed ICF will be filed in the Investigator Site File (ISF). The PIS will contain site contact information in case of any questions or medical emergency.

Any written information given to potential patients will be submitted to, and approved by, the respective Ethics Committee(s) prior to implementation.

The Investigator will maintain a Patient Screening Log to collect information on all patients who sign an ICF regardless of whether or not they meet the study eligibility criteria following completion of the screening evaluations. After completion of Screening, all patients deemed eligible to take part in this study will be entered onto an Enrolment Log.

## Patient Withdrawal

In accordance with the Declaration of Helsinki, the Investigator must explain to the patient that they have the right to withdraw from the study at any time, and that this will in no way prejudice their future treatment. However, unless safety issues occur, we plan to follow the patients for the entire duration of the study in order to analyse efficacy and safety variables also for those patients withdrawing from the study. The reason for any kind of withdrawal must be recorded on the appropriate CRF.

There will be two main categories for withdrawals from the study:

Complete withdrawal:

Stopping investigational product and also continued efficacy and safety evaluations

Standard reasons for withdrawing from further participation in the study and from the follow-up visits

- Patient’s decision (withdrawal of consent to participate)
- Patient lost to follow-up

Withdrawals from investigational product:

Stopping investigational product, but continuing follow-up visits, including efficacy and safety evaluations

Standard reasons for withdrawing from taking further investigational product, but continuing follow-up visits and safety evaluations may be:

- Unacceptable adverse events
- Patient request
- Investigator's discretion
- Patient lost to follow-up/non-attendance
- Intercurrent illness

However, whenever a patient is withdrawn from a study, or for whatever reason is not coming to any further visits, a final study evaluation must be completed for that patient (visit <>) - stating the reason(s) why the patient was withdrawn from the study. All documentation concerning the patient must be as complete as possible. Every effort will be made in order to follow-up and complete patient evaluation. Patients who are withdrawn for any reason will also be evaluated according to the evaluation flow-chart.

Withdrawals due to non-attendance must be followed up by the Investigator to obtain the reason for non-attendance. Withdrawals due to intercurrent illnesses or adverse events must be fully documented in the case record form, with the addition of supplementary information if available and/or appropriate.

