# TREATMENT PROCEDURES

## Overall Study Design

The study is to be performed as a randomized open intervention study. Patient eligibility for the trial will be assessed around 4 weeks after transplantation. If the patient is considered eligible by the Investigator, the patient will attend the Baseline visit (Visit 1, Day 0). At the Baseline visit, the patient will undergo the study-specific evaluations listed in Section 4.3 and will be randomized in a 1:1 ratio to either treatment with paricalcitol or no treatment based on a computer-based allocation sequence.

After the Baseline visit has been completed, the patient will be asked to return to the clinic for the Follow-up visits in the study. The initial Follow-up visits will be the Initial Safety Follow-up visits held every two weeks after the Baseline visit up to Week 6. During these visits to the clinic, blood samples will be taken from the patient for laboratory evaluations and new or changes to pre-existing adverse events will be recorded. After Week 6 up to the final Follow-up visit held at Week 48, the patients will be followed up as per standard clinical practice.

At Week 48 of the study, the patient will return to the clinic for the final Final Follow-up visit (Visit 12, Week 48). This visit will evaluate both efficacy and safety parameters, further listed and described in Section 4.3/Section and Section 4.2, respectively. Every effort will be made in order to follow-up and complete patient evaluation at these Follow-up visits. Patients who are withdrawn for any reason will also be evaluated according to the evaluation flow-chart if possible.

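### The withdrawal section contradicts itself on whether patients who stop for safety reasons stay in follow-up, which could lead to selective loss of the Week 48 outcome, mainly in the paricalcitol arm

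*Protocol*

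**What the plan says.** The Patient Withdrawal section of the protocol contains these rules:

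- **Introduction.** "However, unless safety issues occur, we plan to follow the patients for the entire duration of the study". The stated purpose is to analyse efficacy and safety in withdrawing patients too. What counts as a safety issue is not defined.
- **Complete withdrawal.** Two reasons are listed: "Patient’s decision (withdrawal of consent to participate") and loss to follow-up. Neither is a safety reason.
- **Withdrawal from study drug only.** This category is defined as "Stopping investigational product, but continuing follow-up visits, including efficacy and safety evaluations". Its reasons include "Unacceptable adverse events" and also "Patient lost to follow-up/non-attendance".
- **Closing paragraphs.** For anyone withdrawn or no longer attending, "a final study evaluation must be completed for that patient (visit <>"), with the visit number left blank. Then: "Patients who are withdrawn for any reason will also be evaluated according to the evaluation flow-chart".

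The Overall Study Design section repeats that last rule in a weaker form: "Patients who are withdrawn for any reason will also be evaluated according to the evaluation flow-chart if possible".

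**The concern.** Two rules cover the same patient. The introduction allows follow-up to end when a safety issue arises. The category list keeps a patient who stops drug for an adverse event in all visits. A site that meets this case finds text for either course, and the exemption has no definition to limit it.

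A second fault is independent of the first. A patient who is lost or no longer attends is given as an example of someone who stops drug and goes on attending. That disposition code cannot be applied.

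Other parts of the design make this more than untidy wording. The control arm receives no treatment, so only paricalcitol patients have a study drug to stop. ACR, which measures the primary endpoint, has one scheduled post-baseline value. The Study Populations section removes randomised patients without primary outcome data from the ITT population. If sites used the exemption for drug stoppers, the paricalcitol arm could be thinned selectively while the control arm stayed largely whole. No later analysis can recover urine that was never collected.

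**Working it through.** **Step 1. Which rule applies to a patient who stops paricalcitol because of an adverse event?**

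| Text | Follow-up continues? |
|---|---|
| Patient Withdrawal, introduction | Not assured, if the event is a safety issue |
| Patient Withdrawal, drug-only category | Yes, efficacy and safety |
| Patient Withdrawal, complete-withdrawal reasons | No safety reason listed, so not a complete withdrawal |
| Patient Withdrawal, closing sentence | Yes, whatever the reason |
| Overall Study Design | Yes, but only where possible |

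The introduction conflicts with the category list and the closing sentence. The Overall Study Design wording weakens that closing rule.

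**Step 2. Can another measurement replace Week 48?** The Proteinuria section schedules ACR at baseline and 12 months, and the urine section at baseline and the final visit. The study flow chart marks urine laboratory tests at every visit, but its ACR row marks only the first and last. The compulsory final evaluation for withdrawn patients could supply a value, but its visit field is blank and no content is fixed. The Week 48 visit itself is numbered 12 (Overall Study Design), 4 (Proteinuria) and 10 (Scheduling of Procedures and flow chart), so the blank cannot be filled by inference.

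**Step 3. How large could the effect be?** The plan gives no stopping rate and no stopper outcome, so it has no figure of its own to reproduce here. From the sample size paragraph: planned difference 5.2 mg/mmol, SD 10 (reading the figure after the baseline mean as the SD), correlation 0.5, 70 randomised, hence 35 per arm.

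Let f be the share of the paricalcitol arm lost, and D the lost patients' Week 48 mean minus that of the retained patients. Then

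full-arm mean = (1 − f) × retained mean + f × (retained mean + D) = retained mean + f × D.

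Analysing only the retained patients misses the full-arm mean by f × D. Both f and D are assumptions:

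| f (patients of 35) | D = 2.6 | D = 5.2 | D = 10 |
|---|---|---|---|
| 5% (1.75) | 0.13 | 0.26 | 0.50 |
| 10% (3.5) | 0.26 | 0.52 | 1.00 |
| 20% (7) | 0.52 | 1.04 | 2.00 |

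Entries are in mg/mmol. The extremes are 0.13/5.2 = 2.5% and 2.00/5.2 = 38% of the planned difference. With D = 0 there is no shift.

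**Step 4. Is it a power problem?** Mainly not. Assume a two-sided 5% level and a normal approximation. A change-score comparison has SD 10 × √(2 × (1 − 0.5)) = 10; a baseline-adjusted comparison has SD 10 × √(1 − 0.5²) = 8.66. Going from 35 v 35 to 28 v 35 (20% of one arm lost) lowers power from 58.5% to 53.6% and from 70.9% to 65.8% respectively. These start below the planned 80% for a separate reason: the stated 30 per arm matches a within-arm paired formula, (10 × (1.960 + 0.842)/5.2)² = 29.03, not a two-arm comparison. The present point does not depend on that.

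**The case against.** The strongest reply is that most of the section favours follow-up. Adverse-event stoppers are placed by name among those who continue visits, no safety reason leads to complete withdrawal, the text promises every effort to complete evaluation, and the closing sentence covers all withdrawn patients without exception. Against this stands one loose introductory clause about a plan. This stands as to likelihood: loss is not automatic and may be rare. It does not remove the conflict, because the exemption remains in the text.

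It could also be said that the clause concerns patients leaving the study, not those who only stop drug. But the section treats both categories as withdrawals from the study, so drug-only stoppers are within its reach.

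Four stronger readings are tempting, and the documents do not support them:

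- *A site that ends follow-up at a safety stop is plainly compliant.* It would be following one clause and breaching the category rule and the closing sentence.
- *Outcomes disappear from one arm only.* The exemption is not limited to drug-related events. The flow chart notes record rejection, malignancy and infection, which can occur in controls. Only the stopping of study drug is confined to paricalcitol.
- *A released patient necessarily has no primary outcome.* The ITT definition asks for at least one post-baseline assessment, which the compulsory final evaluation might supply, though its content is not fixed.
- *The same patients leave the safety comparison.* The safety population includes every randomised patient with at least one dose, and adverse events are followed until resolved or as clinically required. The limit of 7 days after the last dose for collecting adverse events is independent of this clause.

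Finally, the lost-to-follow-up overlap has no shown effect on the result, since such a patient's data are missing under either code. That is fair, but the code still cannot be used as written.

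**Conclusion.** The point holds as an inconsistency in the protocol's data-collection rules, with a possible rather than demonstrated effect on the primary comparison. The exemption and the category list cannot both govern a patient who stops drug for an adverse event, and the drug-only category contains a reason that rules out what the category requires.

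The risk is informative loss concentrated in the paricalcitol arm. It follows from the no-treatment control, the single scheduled post-baseline ACR and the ITT exclusion taken together. Its size rests wholly on assumed values: 0.13 to 2.0 mg/mmol if 5–20% of the arm were lost with a mean difference of 2.6–10 mg/mmol. The upper end is demanding, since 10 mg/mmol is the whole planning SD.

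A reader might infer a bias in the drug's favour. That requires stoppers to have higher ACR than the patients who stay, and nothing in the protocol establishes it. If their ACR were lower, the shift would reverse; if it were the same, only a little precision would be lost. The ITT exclusion rule is a separate matter and enters here only as the route by which a missing value leaves the analysis.

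The correction is worth making because it is cheap and a statistical analysis plan cannot supply measurements that were not taken.

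**What to change.** Amend the wording as follows.

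1. In Patient Withdrawal, delete the safety exemption from the introduction. In Overall Study Design, delete the closing qualifier about possibility.
2. State that stopping study drug, for whatever reason, does not end data collection. Week 48 ACR, eGFR and safety laboratory tests are sought from every randomised patient unless consent is withdrawn, the patient dies or the patient is actually lost.
3. Remove loss to follow-up and non-attendance from the drug-only category, leaving loss to follow-up under complete withdrawal.
4. Fill in the blank visit in the final-evaluation rule, and use one number for the Week 48 visit throughout.

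This changes data collection only; it does not touch any decision to stop or continue study drug. The final visit is already scheduled, so the cost is the amendment itself and some effort to obtain Week 48 samples from patients who have stopped drug.

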# TREATMENT PROCEDURES

## Overall Study Design

The study is to be performed as a randomized open intervention study. Patient eligibility for the trial will be assessed around 4 weeks after transplantation. If the patient is considered eligible by the Investigator, the patient will attend the Baseline visit (Visit 1, Day 0). At the Baseline visit, the patient will undergo the study-specific evaluations listed in Section 4.3 and will be randomized in a 1:1 ratio to either treatment with paricalcitol or no treatment based on a computer-based allocation sequence.

After the Baseline visit has been completed, the patient will be asked to return to the clinic for the Follow-up visits in the study. The initial Follow-up visits will be the Initial Safety Follow-up visits held every two weeks after the Baseline visit up to Week 6. During these visits to the clinic, blood samples will be taken from the patient for laboratory evaluations and new or changes to pre-existing adverse events will be recorded. After Week 6 up to the final Follow-up visit held at Week 48, the patients will be followed up as per standard clinical practice.

At Week 48 of the study, the patient will return to the clinic for the final Final Follow-up visit (Visit 12, Week 48). This visit will evaluate both efficacy and safety parameters, further listed and described in Section 4.3/Section and Section 4.2, respectively. Every effort will be made in order to follow-up and complete patient evaluation at these Follow-up visits. Patients who are withdrawn for any reason will also be evaluated according to the evaluation flow-chart if possible.

